## Abstract

**Background::**

A poor or unhealthy diet is responsible for an important fraction of ischemic stroke risk. Adherence to dietary patterns, such as the Mediterranean diet, rich in monounsaturated fatty acids mainly from olive oil, is associated with a lower stroke risk. Furthermore, lowering low-density cholesterol (LDL-C) levels decreases stroke recurrence. Interestingly, Avocado-substituted diets, which are also rich in monounsaturated fatty acids, significantly decrease LDL cholesterol levels. This study aims to evaluate whether a Mediterranean diet based on Avocados reduces LDL-C compared to a low-fat high-complex carbohydrate diet after 3 months of the intervention in patients who had a recent acute ischemic stroke. The trial will also assess safety and feasibility.

**Patients and methods::**

Prospective, randomized open-label, blinded outcome assessment clinical trial. Participants are patients within a month of being admitted with an ischemic stroke, who consent and fulfil the eligibility criteria. Patients are randomly assigned to either diet intervention in a 1:1 ratio on top of the usual secondary prevention treatment. The intervention diet is:

The main efficacy outcome is a reduction in plasma LDL-C levels at 3 months of the dietary intervention. Secondary outcomes include changes in the levels of serum lipid profile and serum inflammation markers, safety, and feasibility. A sample size of 200 patients was estimated to provide 80% power and 5% level of significance (10% loss and 5% crossover) to detect a minimum difference of 4.6 mg/dL in LDL-C after 3 months of intervention.

**Conclusion::**

We hypothesize that an Avocado-based Mediterranean diet will further reduce the levels of LDL-cholesterol at 3 months compared to the control diet, and that the intervention is safe and feasible.

**Registration::**

The study is registered under ADDSPISE at www.clinicaltrials.gov. Identifier NCT03524742. Protocol ID CAS-605 version 3.0 (May 2nd, 2019).

## Introduction

1

Both the Global Burden of Disease project and the INTERSTROKE study have consistently shown that a poor or unhealthy diet is responsible for an important fraction of disability-adjusted life years and population-attributable risk in ischemic stroke.^[1–3]^

Adherence to dietary patterns is associated with better cardiovascular health.^[4]^ Observational studies show that a plant based or “prudent” diet, a Dietary Approaches to Stop Hypertension diet, a Nordic diet and a Mediterranean Diet (MeDi) are associated with reduced stroke risk.^[5–8]^ Furthermore, in the PURE study, 3 to 4 serving/day of fruit, vegetable, and legume consumption was associated with a lower stroke risk.^[9]^

The “Mediterranean Diet” dietary pattern is characterized by plentiful plant foods including fruits, legumes, nuts, cereals, and olive oil as the principal source of fat rich in monounsaturated fatty acids (MUFA), moderate amounts of fish and poultry, moderate to low amounts of dairy products and low red meat, processed meats and pastries with wine consumed in low to moderate quantities usually with meals.^[10]^ A systematic review and meta-analysis showed that greater adherence to the MeDi was associated with 32% lower risk of stroke.^[11]^

Primary cardiovascular and stroke prevention with the MeDi in the PREDIMED study reported that the pooled effect of the Mediterranean diet based on olive oil or nuts was highly protective against stroke.^[12]^ Current American Heart Association guidelines suggest a Mediterranean diet after ischemic stroke (IS) with a recommendation Class IIa, Level of Evidence C, and Canadian guidelines suggest a Mediterranean diet with evidence level B, but secondary stroke prevention studies with diet are lacking and recommendations are based on extrapolations from observational or primary prevention trials.^[13–16]^

MeDi improves lipid profile, insulin sensitivity, glycemic control and decreases blood pressure, and new-onset diabetes, all strong risk factors for stroke.^[17,18]^ Furthermore, there are several beneficial nutrients abundant in the MeDi that could act on inflammatory biomarkers such as adhesion molecules, cytokines, or molecules related to the stability of atherosclerotic plaque.^[19]^ On the other hand, Avocados, although not part of the classical MeDi, are another nutrient-dense source of MUFA, rich in vitamins, minerals, fiber, phytosterols, and polyphenols. A meta-analysis of randomized clinical trials showed that Avocado-substituted diets significantly decrease the levels of total cholesterol (TC), low-density lipoprotein cholesterol (LDL-C), and triglycerides.^[20]^ A comprehensive review on the effect of Avocados concluded that they can be used as dietary supplements for the treatment of different components of the metabolic syndrome.^[21]^ No evidence exists on the effect of Avocados on stroke prevention.

Lowering LDL-C levels prevent ischemic stroke recurrence in an inverse linear relationship, without a floor effect.^[22]^ Interventions to further decrease LDL-C levels show significantly lower recurrence rates of stroke.^[23–26]^

Our primary aim is to demonstrate a reduction in LDL-C in patients who had a recent (1 month) ischemic stroke receiving a MeDi based on Avocados compared to a low-fat high-complex carbohydrate diet after 3 months. Secondary aims include the safety and feasibility of the interventions.

### Objectives

1.1

#### Primary

1.1.1

To show a significant LDL-C reduction in the group receiving an avocado-based MeDi (intervention diet) at 3 months in patients with IS of less than a month from symptom onset, which are receiving standard secondary prevention care, compared to controls receiving low-fat high-complex carbohydrate diet (control diet).

#### Secondary

1.1.2

1)To show an improvement in the serum lipid profile (reduction of TC and triglycerides; increase in high density lipoprotein cholesterol [HDL-C]) in patients with IS receiving the intervention diet compared to the control diet after 3 months.2)To investigate the change in serum inflammation markers in patients with IS receiving the intervention diet compared to the control diet after 3 months.3)To investigate safety of the intervention diet compared to the control diet after 3 months.4)To investigate feasibility, adherence, and acceptability of the intervention diet compared to the control diet after 3 months.

## Methods

2

This protocol is reported according to the Standard Protocol Items: Recommendations for Intervention Trials, and the intervention is reported according to the Template for Intervention Description and Replication checklist and guide.^[27,28]^

### Trial design

2.1

Prospective, randomized, open-label, blinded outcome assessment (PROBE design), investigator-driven, controlled superiority clinical trial.

### Trial population and setting

2.2

Participants are patients within 1 month of an IS admitted to Clínica Alemana de Santiago, who fulfil the eligibility criteria.

### Eligibility criteria

2.3

Patients are included if fulfilling the following inclusion criteria:

(1)Age ≥ 45 years.(2)A recent ischemic stroke (documented cerebral infarction or transient ischemic attack within the past month prior to randomization).(3)One or more of the following cardiovascular risk factors: hypertension, type 2 diabetes mellitus, insulin resistance, dyslipidemia (elevated LDL or total cholesterol), current tobacco use, coronary heart disease, body mass index (BMI) ≥ 25, and family history of premature cardiovascular disease.(4)Informed consent provided.

Patients are not eligible if one or more of the following exclusion criteria are present:

(1)Comorbidities that would interfere with compliance of the interventions or low likelihood of changing dietary habits (i.e., oncological diseases under chemotherapy, institutionalized patients).(2)Known allergy or intolerant to Avocados.(3)Any feeding limitation that could interfere with the dietary intervention such as dysphagia.(4)Mandatory use of drugs for other reasons that can change lipid profile (such as hormonal therapy, antiretroviral therapy, chronic steroids, etc).(5)The possible etiology of ischemic stroke without any of the above-mentioned cardiovascular risk factors: arterial dissection, thrombophilia, cerebral vasoconstriction reversible syndrome, and other infrequent or rare causes such as vasculitis or stroke related to autoimmune diseases.(6)Any concomitant illness with life expectancy of less than 3 months or that would interfere with the outcome assessments and/or follow-up.

### Consent

2.4

A physician investigator invites eligible patients to participate in the trial and obtains written informed consent from the patient or legal guardian. The rational, aims, intervention, risks, benefits, and patient rights are explained in plain language. Data from patients who withdraw from the study will not be used.

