#### Secondary outcomes: all at 3 months

2.8.2

1)Levels of serum lipid profile: Significant reduction in the mean TC and triglycerides and significant increase in mean HDL-C in the intervention diet group compared to the control diet group.2)Improvements in the levels of serum inflammation markers vascular cell adhesion molecule, Intracellular Adhesion Molecule, Interleukin-6, apolipoprotein A and B in the intervention diet group compared to the control diet group.3)Safety: Frequency of AE and SAE by intervention group.4)Feasibility, adherence, and acceptability:a)the proportion of patients who complete the intervention at 3 months and time from symptom onset to intervention as a measure of feasibility;b)median MEDAS score at the end of the follow-up and adequacy of the interventions as assessed by the quantitative evaluation of the food questionnaires at 30, 60, and 90 days (percentage of adequacy) to measure adherence;c)acceptability will be assessed at 90 days using a structured questionnaire.

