### Safety

2.13

Adverse events associated with the intervention diet are collected from the time of consent until the final 3-month follow-up visit for each participant, whether considered related to the intervention study or not. All adverse events are followed up until they are resolved and are adjudicated by an independent investigator. Investigators assess any adverse effects of the interventions by administering a checklist of symptoms, including mouth symptoms, bloating, fullness, indigestion, altered bowel habits, other diet-related symptoms, and any other symptoms. Serious adverse events are defined according to International Good Clinical Practice recommendations.^[32]^ Safety specifically include all cardiovascular events (acute myocardial infarction, any stroke, cardiovascular procedures, and cardiovascular deaths) and deaths. All patients are adjudicated by an independent investigator and handled by the treating physician.

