### Statistical analyses

2.17

All efficacy analyses will be performed according to the intention-to-treat principle. The primary outcome will be compared between the 2 groups by an analysis of covariance adjusting for baseline measures unbalanced by randomization and with baseline LDL-C and statin use (initial and final doses) as covariables. To account for missing data, multiple imputations using chained equations will be used, assuming randomness. The results will be compared to those with complete data. A sensitivity analysis will be carried out to investigate the robustness of the findings according to adherence to the intervention. Safety analysis will be performed for all patients participating in the study. The number of patients with AEs, the occurrence of specific SAEs, and discontinuation due to SAEs will be tabulated. Binary outcomes, such as AEs, major cardiovascular events (acute myocardial infarction, stroke, or vascular death), or death will be analyzed with the Chi-2 test for independence. Analysis of adherence will be performed in all patients who finalized the study. The proportion of patients who completed the intervention at 3 months will be analyzed using the Chi-2 test for independence. The percentage of adequacy of the diet intervention at 1, 2, and 3 months will be analyzed with generalized linear mixed models for repeated measures. Feasibility assessed as the mean time from symptom onset to intervention will be analyzed using Student's *t* test. Analysis of the acceptability 14-item questionnaire will be performed in all patients completing the follow-up with the Mann–Whitney–Wilcoxon non-parametric test. Exploratory subgroup analyses will be carried out irrespective of whether there is a significant treatment effect on the primary outcome. These analyses will be adjusted for confounders. The following pre-specified subgroup analyses will be performed by adding an interaction term to the models: age (< or ≥ mean) years, sex, education level < or ≥12 years, post-stroke disability (modified Rankin score < or ≥1), physical activity (Rapid Assessment of Physical Activity questionnaire score < or ≥6), MEDAS score (< or ≥ median), dyslipidemia (yes/no), diabetes/insulin resistance (yes/no), BMI (< or ≥25), and BMI (< or ≥30). Per protocol analysis will be performed for the primary and key secondary efficacy outcomes, using the same statistical test as per the intention-to-treat analysis.

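### The consent section's rule that withdrawn patients' data are not used contradicts the intention-to-treat, imputation, safety and completion analyses

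*Protocol article*

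**What the plan says.** Section 2.4 (Consent) ends with the rule: "Data from patients who withdraw from the study will not be used". It does not restrict the rule to data that would arise after withdrawal, or to patients who ask for their records to be erased.

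Other sections make commitments that involve the same patients:

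- Section 2.17 (Statistical analyses), efficacy: "All efficacy analyses will be performed according to the intention-to-treat principle".
- Section 2.17, missing data: "To account for missing data, multiple imputations using chained equations will be used, assuming randomness". The imputed result is then set against the complete-data result.
- Section 2.17, safety: "Safety analysis will be performed for all patients participating in the study". Among the outputs, "discontinuation due to SAEs will be tabulated".
- Section 2.13 (Safety): "Adverse events associated with the intervention diet are collected from the time of consent until the final 3-month follow-up visit for each participant".
- Section 2.8.2 (Secondary outcomes) takes as a feasibility outcome "the proportion of patients who complete the intervention at 3 months". Section 2.17 compares it between arms with a chi-squared test.

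Section 2.11 encourages patients who do not follow their diet to remain in the study. Not adhering is therefore distinct from leaving. No section says how the rule in 2.4 fits with the others.

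**The concern.** An analyst cannot obey section 2.4 and section 2.17 together. If 2.4 prevails, the efficacy population becomes those who were randomised and did not withdraw, which is a selection made after allocation. Participants know their diet, and the arms receive different foods and different food payments (section 2.12), so withdrawal may well differ by arm.

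The direct losses are in safety and feasibility, both stated secondary aims. A patient who leaves because of an adverse event takes that event out of the tables. A patient who leaves for any reason stops counting as a non-completer. The Discussion describes the trial as a pilot for a phase 3 design, so an overstated completion rate and an undercounted event rate would carry forward.

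This is not a detail left to a separate analysis plan. The rule is stated, and it conflicts with other stated rules.

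**Working it through.** **1. What each analysis needs, and what the rule leaves**

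| Planned analysis | Needs from a withdrawn patient | Under section 2.4 |
|---|---|---|
| Intention-to-treat (2.17) | membership of the randomised arm | excluded |
| Multiple imputation (2.17) | baseline LDL-C, statin dose, 30- and 60-day diet recalls (Table 1) | deleted |
| Safety tables (2.13, 2.17) | adverse events recorded from consent, including the 30- and 60-day questionnaires | deleted |
| Discontinuation due to SAEs (2.17) | the event and the reason for leaving | deleted if the patient withdrew |
| Completion proportion (2.8.2, 2.17) | a place in the denominator | removed |

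**2. Completion proportion**

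Inputs: 200 randomised, 100 per arm, and 10% loss (section 2.16).

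- Loss: 200 × 0.10 = 20, which leaves 180 completers.
- All randomised patients in the denominator: 180/200 = 90%.
- All 20 are withdrawals and the rule is applied: 180/(200 − 20) = 180/180 = 100%.
- Only 10 of the 20 are withdrawals (assumption): 180/(200 − 10) = 180/190 = 94.7%.
- None are withdrawals: 180/200 = 90%, so the rule does nothing.

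If every non-completer were a withdrawal, true completion of 190/200 = 95% or 170/200 = 85% would also read 100%.

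The comparison between arms suffers too. Suppose the 20 are all withdrawals, split 15 and 5 between the arms (assumption). With all patients kept, 85/100 is compared with 95/100:

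χ² = 200 × (95×15 − 85×5)² / (100 × 100 × 180 × 20) = 200 × 1000² / 36,000,000 = 5.56,

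against a 5% critical value of 3.84. Under the rule the same data read 85/85 and 95/95, and the test has nothing to compare.

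**3. Primary LDL-C difference**

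Table 1 schedules study blood only at baseline and 90 days, so a patient who leaves before day 90 has no final LDL-C to delete. The question is therefore how deletion followed by the planned analysis of covariance compares with keeping everyone and imputing.

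This was simulated with assumed inputs: true difference −4.6 mg/dL; about 10% withdrawal in the intervention arm only; log-odds of withdrawal rising by 0.5 to 1.0 per SD of LDL-C; SD 10.5 or 25; baseline-to-final correlation 0, 0.5 or 0.7; baseline LDL-C as the only covariate and the only imputation predictor. SD 10.5 is roughly what 100 per arm implies at 80% power: with 90 per arm and the difference cut by 5%, 4.37 / [(1.960 + 0.842) × √(2/90)] ≈ 10.5. SD 25 is an assumption.

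Results at log-odds 1.0 and correlation 0.7, with withdrawal driven by final LDL-C:

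| SD | Unadjusted completers | Covariance analysis after deletion | Imputation of all randomised |
|---|---|---|---|
| 10.5 | −5.53 | −5.08 | −5.07 |
| 25 | −6.83 | −5.76 | −5.75 |

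When withdrawal depends on baseline LDL-C instead, both planned-type analyses return about −4.6 (range −4.55 to −4.64). Over all 24 settings, deletion and imputation differed by at most 0.02 mg/dL. A separate run of the SD 25 case gave −5.79 and −5.82, a gap of 0.03.

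The reason is simple. Imputing final LDL-C from the completers' regression on baseline places the missing patients on the line that the covariance analysis already fits, so the adjusted difference hardly moves.

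**The case against.** **A narrower reading is plausible.** The sentence sits in the consent section, straight after patients' rights, and may be meant only as a promise to people who revoke permission to use their data. Section 2.17 does separately promise safety in all participating patients. The full protocol or consent form, not shown, may define withdrawal. This stands as a reason to clarify the sentence, but the text itself carries no such limit.

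**The feasibility and safety outcomes are not emptied.** A reader might infer that imputation has nobody left to impute and that completion must come out near 100%. The documents do not support that. Patients who die, are lost to follow-up or stop the diet but stay in the study remain in the data and still count as non-completers. Section 2.16 assumes 10% loss, which is not the same as 10% withdrawal. The 100% figure is the extreme case.

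**The primary comparison.** A reader might also infer that the rule shifts the LDL-C difference by a definite amount, such as the move from −4.6 to −6.83 in an unadjusted completer comparison. That is not the planned analysis. The bias that remains after adjustment comes from withdrawal linked to a final LDL-C nobody observed, and imputation from baseline leaves it in place. Keeping the 30- and 60-day recalls as auxiliary variables might help somewhat, but this was not quantified.

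**Conclusion.** The rule is wrong as written. It contradicts the intention-to-treat and imputation plan, the safety analysis of all participating patients, the table of SAE-related discontinuations and the completion outcome, and nothing in the article reconciles them.

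Its definite consequences are a post-randomisation exclusion in an open-label trial, the loss of withdrawn patients' adverse events, and a completion denominator that omits them. On the plan's own 10% loss, completion is overstated by 0 to 10 percentage points, depending on how much of that loss is formal withdrawal. The article gives no number of withdrawals.

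No specific bias in the primary LDL-C difference is claimed. Deletion and baseline imputation agree within about 0.03 mg/dL under the assumptions above, and bias from withdrawal that depends on unobserved final LDL-C persists under both.

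**What to change.** Replace the sentence in section 2.4 with wording to this effect: no new data are collected after consent is withdrawn; data collected before withdrawal are kept and analysed in the randomised arm, unless the participant asks for erasure or was promised it. State explicitly that stopping the diet is not withdrawal from the study, as section 2.11 already implies.

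Then align sections 2.8.2, 2.13 and 2.17:

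- Keep all randomised patients in the intention-to-treat set, the imputation model, and the completion and safety denominators.
- Make the 30- and 60-day data available as auxiliary variables for imputation.
- Report withdrawals, and any erased records, by arm with reasons.

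The cost is protocol and consent wording and an ethics notification. No extra patients or visits are needed. Section 2.20 describes the trial as still randomising, so on that status the change can be made before analysis.

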### Randomization

2.5

Eligible patients are randomly assigned in a 1:1 ratio by study personnel to either diet intervention, using a desktop minimization program (MinimPy 0.3, Python Software Foundation), balanced by sex, age group <70 and ≥70 years (this is the median age of patients admitted with stroke in Clínica Alemana), and previous adherence to a Mediterranean diet as defined according to the Mediterranean Diet Adherence Screener (MEDAS) score <7 or ≥7 (this is the median score found in stroke patients in our institutional registry) (Fig. 1).^[29,30]^

**Figure 1 F1:**
[figure not shown]
Flow diagram of the study.

### Masking

2.6

Participants and investigators are not masked to the intervention diets; however, outcome assessors of LDL-C and other laboratory results, and data analysts are masked to the diet allocation. Unblinding is not anticipated.

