### Measurements

2.10

Anthropometric measurements are performed by a study nurse or a study nutritionist according to the study schedule (Table 1). Weight and height are measured by using standard calibrated scales, respectively; waist circumference midway between the lowest rib and the iliac crest by using an anthropometric tape, and blood pressure after 10 minutes of rest in triplicate with a standard calibrated sphygmomanometer.

Blood samples are collected following overnight fasting for at least 10 ± 2 hours, at baseline and at 3 months, coded, centrifuged, and processed in the morning (lipids) at Clínica Alemana or stored at <80°C until assayed (for inflammatory biomarkers, see supplement) at The Medical Chemistry Center, Universidad del Desarrollo. Total cholesterol, LDL-C, HDL-C, and TG are processed with a homogeneous enzymatic colorimetric test in the chemistry automatic analyzer COBAS 8000 platform (Cobas, Roche Diagnostics) upon arrival to the laboratory. All tests are performed according to the manufacturer's instructions. The laboratory technicians are masked to the interventions. Analyses are performed for each participant in frozen samples of whole serum or plasma, as appropriate. Details of the analysis are provided in the Supplementary Material.

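### The trial is labelled blinded outcome assessment without limit, but the independent adjudicator of adverse and vascular events is not among the masked roles

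*Protocol article*

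**What the plan says.** Section 2.1 (Trial design) describes the study as "Prospective, randomized, open-label, blinded outcome assessment (PROBE design), investigator-driven, controlled superiority clinical trial". The Abstract uses the same label, also without restricting it to particular outcomes.

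Section 2.6 (Masking) states who does and does not know the diet: "Participants and investigators are not masked to the intervention diets; however, outcome assessors of LDL-C and other laboratory results, and data analysts are masked". Section 2.10 (Measurements) repeats the laboratory part: "The laboratory technicians are masked to the interventions".

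Section 2.13 (Safety) says of adverse events: "All adverse events are followed up until they are resolved and are adjudicated by an independent investigator". After listing the cardiovascular events and deaths that count as safety outcomes, it adds: "All patients are adjudicated by an independent investigator and handled by the treating physician". That sentence presumably means the patients' events. Neither sentence says whether this person is masked.

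Section 2.8.2 makes the frequency of adverse and serious adverse events by group a secondary outcome. Section 2.17 plans chi-square tests for adverse events, major cardiovascular events and death.

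**The concern.** A reader who sees the design label will take it that outcomes needing judgement are classified by someone who does not know the diet. The only people section 2.6 masks are those handling laboratory values and those analysing the data. Masked analysts do not help if an event was already classified by someone who knew the arm.

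Safety is a stated secondary objective, and the Abstract's hypothesis includes the claim that the intervention is safe. Several safety components depend on judgement: a new stroke in a patient who had one within the past month, vascular versus non-vascular death, and digestive or other symptoms from the checklist. If the adjudicator knows the diet, borderline cases may be read differently in the two arms. The bias could run in either direction, and the planned test would not reveal it.

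**Working it through.** The article states no figure on this point, so the main check sets the sections side by side.

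1. **Scope of the label.** Section 2.1 and the Abstract apply blinded outcome assessment to the trial as a whole.
2. **Masked roles.** Sections 2.6 and 2.10 name laboratory assessors, laboratory technicians and data analysts. No event adjudicator appears.
3. **Unmasked roles.** Section 2.6 names participants and investigators.
4. **The adjudicator.** Section 2.13 calls this person an independent investigator. By function the role is absent from the masked list. By title it falls in the unmasked group. Independence from the study team does not mean ignorance of the allocation.
5. **Steps before adjudication.** Section 2.7 has the nutritionist who counsels on the allocated diet ask about adverse events, and a physician investigator collect them at the closing session. Section 2.13 has investigators administer the symptom checklist. All of these people know the diet, so adjudication is the safety step at which masking is most practicable.
6. **Use of the result.** Sections 2.8.2 and 2.17 compare the events by arm.

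**How much could classification matter?** The article gives no event rates and no misclassification rates, so every rate below is an assumption. Only the 100 per arm (section 2.16) and the two-sided 5% level (section 2.17) come from the plan or follow from it.

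*Common events.* Let the true risk p be equal in both arms, and let a share 1 − k of events in one arm be under-classified, so that p₁ = p and p₂ = kp. With p̄ the mean of p₁ and p₂, and n = 100 per arm, the chance of a significant result favouring that arm is approximately

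Φ{ [(p₁ − p₂) − 1.96·√(2p̄(1 − p̄)/n)] / √[(p₁(1 − p₁) + p₂(1 − p₂))/n] }.

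For p = 0.20 and k = 0.8: p₂ = 0.16 and p̄ = 0.18, giving (0.04 − 1.96 × 0.0543)/0.0543 = −1.23 and Φ ≈ 0.11.

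For p = 0.40 and k = 0.8: p₂ = 0.32 and p̄ = 0.36, giving (0.08 − 1.96 × 0.0679)/0.0676 = −0.78 and Φ ≈ 0.22.

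| Assumed true risk | 10% under-classified | 20% under-classified |
|---|---|---|
| 5% | 3.6% | 5.3% |
| 20% | 5.5% | 11% |
| 40% | 8.4% | 22% |

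The nominal rate in that direction is 2.5%.

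*Rare vascular events.* Suppose both arms have the same count and two borderline events in one arm are not counted.

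| Assumed count per 100 | After two calls | Relative change | Chi-square p (uncorrected) |
|---|---|---|---|
| 3 v 3 | 3 v 1 | 2/3 = 67% | about 0.31 |
| 5 v 5 | 5 v 3 | 2/5 = 40% | about 0.47 |
| 7 v 7 | 7 v 5 | 2/7 = 29% | about 0.55 |

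For 5 v 3, z = 0.02/√(2 × 0.04 × 0.96/100) = 0.72. The tabulated contrast moves, but the test result at 5% does not.

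**The case against.** The strongest reply is that the article is silent on the adjudicator rather than wrong. A reader might infer from section 2.6 that the adjudicator sees the allocation. No sentence says so, and the word investigators there could mean only the trial team, from whom section 2.13 separates an independent person. This stands as a limit: the fair statement is that the adjudicator is not listed as masked and, on the text, falls in the unmasked group.

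It can also be said that the article condenses a fuller protocol that is not shown, and that redaction of event files is operational detail. The exact procedure may well be written there. But section 2.6 does state which roles are masked and which are not, and that statement does not support the unrestricted label in section 2.1.

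A reader might further infer that the blinded-outcome label is false, or that the efficacy result is at risk. Neither follows. LDL-C and the other laboratory outcomes are assessed masked, and section 2.6 is open about this scope.

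Nor does knowledge of the diet decide whether an event counts by way of attribution. Section 2.13 collects events regardless of suspected relation to the intervention, seriousness follows a standard definition, and all-cause death leaves little room for judgement. What remains exposed is the classification of event type and of borderline symptoms.

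Finally, masking the adjudicator would not touch reporting by participants or collection by unmasked staff, which may be the larger source of bias. That is correct, and it limits what the change can achieve.

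**Conclusion.** The point holds in a limited form. The design label covers all outcomes, while the stated masking covers only laboratory outcomes and data analysis. The adjudicator of safety events is not among the masked roles, so the classification of stroke, vascular death and symptom-type events compared by arm is open to bias. Primary efficacy is unaffected.

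The size is unknown. The 11% and 22% illustrations rest on an assumed 20% one-sided under-classification of common events. With 10% the figures are about 5.5% and 8%. For rare vascular events a shift of 29% to 67% in one arm's count may look alarming, but it rests on two assumed calls at assumed event rates and would not change the planned test at 5%. None of these figures shows that bias has occurred. The case for a change is that the role already exists and masking it is cheap.

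**What to change.** Add the independent adjudicator to the masked roles in section 2.6. State that this person receives event records with the allocation and references to the diet removed. Apply this to all remaining events and, where feasible, have earlier events re-read from redacted files, since randomization began in August 2018 and was still under way when the article was written. If the adjudicator is already masked in practice, one sentence saying so settles the matter. If masking cannot be arranged, restrict the blinded-outcome label to the laboratory outcomes and report open classification as a limitation of the safety comparison.

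The cost is a little coordinator time to prepare the files, plus any re-reading of earlier events, and no new staff. Masking will be only partial for diet-related symptoms, which can reveal the arm. Reporting bias from unmasked participants, nutritionists and investigators will remain and should be acknowledged.
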